### Statistical analyses

A customized online database will be used to manage data and SPSS version 25.0 will be used for all analyses. Group t-test, Mann-Whitney u test or χ2 test will be conducted for comparisons between two groups according to different types of variables. Occurrence of delayed-onset and early-onset PSCI will be analyzed as categorical data (yes or no). χ2 test will be used to compare the incidence between two groups and multivariate logistic regression will be used to adjust confounders. Paired sample t-tests or Wilcoxon matched-pairs signed-ranks test will be used to compare WMH degree (visual scale scores and WMH volume) and total cognitive scores at different time point within each group. Changes of WMH degree (indicating degeneration) and total cognitive scores from baseline to 24 weeks will be compared between two groups using Group t-test or Mann-Whitney u test and multivariate linear regression will be used to explore the contributing factors. Changes of cognitive scores will further be dichotomized as improved and unimproved group to do the analysis, improvement is defined as score change < 0 for Alzheimer’s Disease Assessment Scale-Cognitive subscale or > 0 for Montreal cognitive assessment scale. Furthermore, Kaplan–Meier analysis and cox proportional hazards analysis will also be performed to compare the incident rate of any cognitive impairment between two groups and explore contributing factors. Two-sided value of *p* < 0.05 will be considered significant.

Outcomes will be measured both for intention-to-treat population (main analysis population) and the per protocol population. The intention-to-treat population consist of those who have a complete baseline assessment as well as at least one follow-up assessment for the primary outcome variables. Missing values of cognitive scores will be replaced by last observation carried forward method. The per protocol population consist of those who complete the 24-week follow-up with no major protocol violations.

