## Background

Post stroke cognitive impairment (PSCI) indicates cognitive impairment resulting from a stroke event, including post stroke dementia (PSD) and PSCI not fulfilling criteria for dementia [1]. Most PSCI occur in the early stage after stroke (early-onset PSCI), while some patients without early-onset PSCI will develop cognitive impairment months after stroke (delayed-onset PSCI) [2–5]. Data of the prevalence of delayed-onset PSCI (including PSD and PSCI not fulfilling criteria for dementia) is still in lack, while the prevalence of delayed-onset PSD varies largely from 4.4 to 23.9% according to a systematic review [6]. Though it seems lower comparing with early-onset PSD, the risk of dementia is still 1.6 to 10.3 times higher than that in stroke-free population. Study of these group of patients is important because there might be different mechanism from early-onset PSCI, which leads to a different optimal treatment plan.

Studies showed that early-onset PSCI mainly resulted from acute stroke lesions [7], while delayed-onset PSCI was found specifically associated with presence of severe cerebral small vessel diseases (CSVD) at baseline [6, 8]. Nevertheless, recent longitudinal studies have further indicated that the primary mechanism may be cerebral secondary degeneration (CSVD progression presented as increased white matter hyperintensity and cerebral atrophy) induced by acute stroke apart from baseline co-existent CSVD [9–11]. However, no interventional researches have been conducted to testify the role of secondary degeneration in its mechanism.

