### Sample size

Previous studies showed that the prevalence of delayed-onset PSD ranged from 4.4 to 23.9% [6]. We chose 4.4, 10.0 and 23.9% with the hypothesized effect size of 20, 30, and 50% reduction for NBP to do the calculation [21]. Considering the feasibility, 4.4% of the incident rate and reduction of 50% were used in the end, then 1200 cases for per group could meet the statistical requirement. A drop-out rate of 20% was also considered, then 3000 cases in total were required.

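### Change in white-matter and cognitive scores is compared between arms without adjusting for the baseline value: valid, but less precise than an ANCOVA on data already collected

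*Protocol article*

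**What the plan says.** All points are from the protocol article.

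- **Secondary outcomes.** Under Statistical analyses, changes in WMH (visual score and volume) and "total cognitive scores from baseline to 24 weeks will be compared between two groups using Group t-test or Mann-Whitney u test". The same sentence goes on to a multivariate linear regression, whose stated purpose is to explore which factors contribute. No baseline term is named.
- **Split at zero.** "Changes of cognitive scores will further be dichotomized as improved and unimproved group to do the analysis", with any movement in the favourable direction on ADAS-Cog or MoCA counted as improvement.
- **Primary outcome.** "χ2 test will be used to compare the incidence between two groups and multivariate logistic regression will be used to adjust confounders". The covariates are not named, and the text does not say which of the two results is the main one. "Two-sided value of *p* < 0.05 will be considered significant" applies throughout.
- **What is collected.** The Design section and the schedule (Fig. 2 legend) place cognitive tests and brain MRI at baseline and at 24 weeks. The main analysis population is defined to require a complete baseline assessment.
- **Prognosis.** The Background says that "delayed-onset PSCI was found specifically associated with presence of severe cerebral small vessel diseases (CSVD) at baseline".

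**The concern.** A change score gives the baseline a fixed weight of one. That weight is right only if the baseline predicts the week-24 value one for one. Otherwise, subtraction carries baseline noise into the outcome. ANCOVA estimates the weight from the data, and in large samples it is never less precise than the change score when the SDs and correlation are similar in the two arms.

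The document itself gives a reason to expect a noisy cognitive baseline. Baseline testing takes place within two weeks of stroke, and the Discussion doubts an earlier small trial because cognition measured soon after stroke may be distorted by transient delirium.

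What is at stake is the precision of the secondary comparisons. These include the WMH comparison, which the Discussion relies on to test the secondary-degeneration hypothesis. For the primary outcome the issue is narrower: two analyses of the same endpoint stand side by side without a stated order.

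**Working it through.** **Continuous secondary outcomes**

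Inputs: n = 1200 per arm (Sample size, after drop-out); two-sided alpha 0.05 (Statistical analyses). Two assumptions are needed: equal SD σ at baseline and week 24, and a baseline-to-week-24 correlation r. The document gives no r, so a range is shown.

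Variance of the estimated difference between arms:

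- change score: (2/n) × 2σ²(1 − r)
- ANCOVA: (2/n) × σ²(1 − r²)
- ratio: (1 − r²) / [2(1 − r)] = (1 + r)/2

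The last column is the power of ANCOVA for an effect at which the change-score t-test has 80% power.

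| r | ratio (1 + r)/2 | variance saved | ANCOVA power |
|---|---|---|---|
| 0.3 | 0.65 | 35% | 93.5% |
| 0.5 | 0.75 | 25% | 89.9% |
| 0.7 | 0.85 | 15% | 86.0% |
| 0.8 | 0.90 | 10% | 84.0% |
| 0.9 | 0.95 | 5% | 82.0% |

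Below r = 0.5 the change-score variance 2σ²(1 − r) exceeds σ². Subtracting the baseline is then worse than ignoring it. Above r = 0.5 subtraction helps, but less than ANCOVA does.

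**Primary outcome**

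Inputs from Sample size: "4.4% of the incident rate and reduction of 50% were used in the end", so 4.4% against 2.2%; 1200 evaluable patients in each arm; and for attrition, "A drop-out rate of 20% was also considered, then 3000 cases in total were required".

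- *The plan's own figures.* The drop-out step reproduces exactly: 2400 / (1 − 0.20) = 3000. Power is not stated. The two-sided pooled formula gives 1034 per group at 80% power, 1183 at 85% and 1384 at 90%, so 1200 fits about 85% power (85.5% by the formula).
- *Expected events.* 1200 × 0.044 + 1200 × 0.022 = 52.8 + 26.4 ≈ 79.
- *Gain from adjustment.* Simulated power with 1200 per arm, one baseline covariate of assumed strength and 3000 simulated trials per row (Monte Carlo standard error about 0.6 points):

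| assumed OR per SD of covariate | χ2 | adjusted logistic |
|---|---|---|
| 1.65 | 86.9% | 86.9% |
| 2.2 | 86.6% | 87.2% |
| 2.7 | 84.5% | 86.7% |
| 4.5 | 86.4% | 89.9% |

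The gain runs from about 0 to 3.5 points. The top of that range needs a very strong predictor.

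**The case against.** Several stronger readings are tempting, and the document does not support them.

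- *The plan is unadjusted throughout and discards baseline data.* It does not. An adjusted logistic model is stated for the primary outcome, a Cox model is planned for any cognitive impairment, and a change score uses the baseline by subtraction.
- *The comparisons are biased.* Randomisation makes the unadjusted tests valid. Chance baseline imbalance is also small at this size: its SD is √(2/1200) ≈ 0.04 baseline SDs. At r = 0.5 an imbalance of that size moves the change-score contrast by about (1 − 0.5) × 0.04 = 0.02 SDs.
- *The secondary outcomes are underpowered.* The trial is sized for a rare binary event. With 1200 per arm, the change-score t-test has 80% power for (1.96 + 0.84) × √(2/1200) ≈ 0.11 SDs of change.
- *Covariates will be picked after seeing the data.* The text leaves this open but does not say it. A covariate list is the kind of detail that a condensed article leaves to an analysis plan.
- *The split at zero loses information.* Cutting a normal outcome at its median keeps 2/π ≈ 0.64 of the information, but the cut here is at zero change, and the split is added to the continuous analysis rather than replacing it.
- *Each centre holds its own list, so centre must be in the model.* Under Randomization, the code list goes to the investigators in every centre. Stratification by centre is not stated.

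The objection also has force on size. If r is near 0.9, which could be so for WMH volume over 24 weeks (an assumption), the saving is only 5%.

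One part of the point survives all of this. The between-group test for the continuous outcomes is stated, not left open, and it is the less efficient one. An unseen analysis plan could add covariates, but it would have to depart from this text to change the test.

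**Conclusion.** The point holds as one of efficiency on the secondary outcomes, and it is modest. The stated comparison of change in WMH and cognitive scores is valid, but its variance is higher than it need be. ANCOVA would remove 25% of it at r = 0.5, 15% at 0.7 and 5% at 0.9, assuming equal SDs at the two times. The gain is probably larger for the cognitive scores, given the early baseline, than for WMH volume; that ordering is a judgement, since the document has no correlation to check it against.

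For the primary outcome the point is only that the order of the χ2 test and the logistic model should be stated. A reader might infer that much power is lost by leading with χ2; at about 0 to 3.5 points, it is not. The figure of about 79 events rests on the planning rates. The 4.4% is a rate for dementia, whereas the endpoint also counts mild impairment, so the actual number may be higher.

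**What to change.** 1. **Secondary outcomes.** Make the main between-group analysis of MoCA, ADAS-Cog and WMH an ANCOVA of the 24-week value on arm and baseline value. Using change as the response gives the same treatment estimate once baseline is in the model. Analyse WMH volume on the log scale, at both times, if it is skewed.
2. **Improved/unimproved split.** Report it as description only.
3. **Primary outcome.** State before the data are seen whether χ2 or the adjusted logistic model is decisive, with the other as supportive. If the model decides, name a short baseline set that includes baseline WMH, since the Background singles out baseline small vessel disease. About 79 expected events do not comfortably support a long covariate list together with an unknown number of centres. A standardised risk difference from that model would match a primary outcome framed as a difference in incidence.

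The cost is wording in the analysis section. The baseline scores and MRI are already scheduled, and no change to sample size or visits is needed.

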## Methods

### Design

Effects of NBP on Delayed-onset Post Stroke Cognitive Impairment (End-PSCI) is a prospective, parallel-group, open-label, multicenter, randomized controlled trial with blinded outcome assessment. Hospital patients within 2 weeks of cerebral infarction onset will be randomized into either standard medical therapy group or standard medical therapy combined NBP treatment group. A set of validated cognitive tests and blood samples collection will be implemented at acute phase (within 2 weeks of onset), 6 weeks, 12 weeks and 24 weeks after stroke. Brain magnetic resonance imaging (MRI) including T1, T2 and T2 Fluid-attenuated inversion recovery imaging (most are clinical routine scans with some high resolution, isotropic scans) will also be performed at acute phase and 24 weeks after stroke. An independent Data and Safety Monitoring Board (DSMB) will regularly monitor safety during the study. The trial has been approved by the Institutional Review Board/Ethics Committee in the First Affiliated Hospital of Xi’an Jiaotong University (approval number: XJTU1AF 2020LSK-032). Figure 1 this study is ongoing (recruitment not completed) at the time of submission.

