### Secondary outcomes

The difference of white matter degeneration between two groups after 24 weeks. The degeneration will be reflected by changes of visual scale scores (modified Scheltens Visual Scale) [26] and white matter hyperintensity (WMH) volume from baseline to 24 weeks.The difference of cognitive score changes from baseline to 24 weeks between two groups. Cognitive testing includes Montreal Cognitive Assessment, Beijing Version (MoCA-BJ) [27], Alzheimer’s Disease Assessment Scale-Cognitive Subscale, Chinese version (ADAS-Cog-C) [28], Hamilton depression Rating scale (HAMD-17) [29] and Activities of Daily Living Scale (ADL), Chinese version [30].The difference of prevalence of early-onset PSCI between two groups after 24 weeks. Early-onset PSCI is defined as cognitive impairment including mild cognitive impairment and dementia developed within 3 months after stroke and persistently existed at least for 3 months.

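### Carrying scores forward in the main cognitive-score comparison can bias the week-24 difference; a repeated-measures model is a cheap improvement for this secondary outcome

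*Protocol article*

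**What the plan says.** All references are to the protocol article.

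- **Visits (Design):** cognitive tests are done "at acute phase (within 2 weeks of onset), 6 weeks, 12 weeks and 24 weeks after stroke".
- **Endpoint (Secondary outcomes):** "The difference of cognitive score changes from baseline to 24 weeks between two groups". The scales listed are MoCA-BJ, ADAS-Cog-C, HAMD-17 and ADL.
- **Comparison of arms (Statistical analyses):** changes in "total cognitive scores from baseline to 24 weeks will be compared between two groups", by a two-sample t-test or a Mann-Whitney test. Linear regression on the same change is there to explore contributing factors, and the change is also split into improved and unimproved.
- **Other use of the scores (same section):** paired tests of "total cognitive scores at different time point within each group".
- **Missing data (same section):** "Missing values of cognitive scores will be replaced by last observation carried forward method".
- **Main population (same section):** intention to treat, needing a "complete baseline assessment as well as at least one follow-up assessment for the primary outcome variables". A per-protocol set of 24-week completers is analysed as well.

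**The concern.** In the comparison between arms, the week-6 and week-12 scores enter only as substitutes for a missing week-24 score. One follow-up visit is enough to be in the main population, so a patient last seen at week 6 is analysed as if nothing had changed by week 24.

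That is doubtful in this trial for two reasons.

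- **The effect may change over time.** Primary outcome defines delayed-onset impairment as developing 3 to 6 months after stroke. A score from week 6 or 12 falls before that window or at its start, so carrying it forward leaves out the period in which a benefit of NBP is expected.
- **Drop-out is sizeable and may be unbalanced.** Sample size allows 20%. Under Interventions, a transaminase rise on NBP leads to withdrawal and counts as drop-out, which can happen only on NBP. Starting certain cognition-affecting drugs also counts as drop-out in either arm (Interventions, Discussion). If NBP works, that rule would remove more controls.

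At stake are the estimate, interval and test for a named secondary outcome.

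**Working it through.** **Figures in the plan.** No power or sample size is stated for the score comparison. Sample size supplies only the numbers: 2 × 1200 / (1 − 0.20) = 3000, so 1500 per arm, and 20% drop-out.

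**Assumptions (not in the documents).** Score SD 1, with higher meaning better. Visit correlations 0.60 to 0.82. Mean recovery of 0.30 SD from week 6 to 24, with week 12 halfway (0.15 SD still to come). True effect 0 / 0.05 / 0.10 SD at weeks 6 / 12 / 24. Drop-out unrelated to scores, half after week 6 and half after week 12.

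**Expected LOCF estimate.** Let d_C and d_N be the drop-out proportions in control and NBP. A proportion d/2 carries week 6, d/2 carries week 12, and 1 − d has week 24.

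- Effect lost in NBP: (d_N/2)(0.10 − 0) + (d_N/2)(0.10 − 0.05) = 0.075 d_N
- Recovery lost unequally: (d_N − d_C)/2 × (0.30 + 0.15) = 0.225 (d_N − d_C)
- Estimate = 0.10 − 0.075 d_N − 0.225 (d_N − d_C)

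| Drop-out, control / NBP | Arithmetic | LOCF estimate (SD) |
|---|---|---|
| 20% / 20% | 0.10 − 0.015 − 0 | 0.085 |
| 15% / 25% | 0.10 − 0.01875 − 0.0225 | 0.059 |
| 25% / 15% | 0.10 − 0.01125 + 0.0225 | 0.111 |

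If the effect is constant at 0.10 SD, the first loss vanishes. With equal drop-out the second vanishes too, and the estimate is 0.100. If scores were falling rather than recovering, the second term would change sign.

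**Power at 20% / 20%.** With a baseline to week-24 correlation of 0.60, the SD of change is √(2 × 0.40) = 0.894 and the standard error is 0.894 × √(2/1500) = 0.0327. Then z = 0.085 / 0.0327 = 2.60, and power is Φ(2.60 − 1.96) = 0.74. Simulations gave 73-76% for the planned test and 87-89% for a likelihood estimate using all visits, which recovered 0.100 SD.

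**Rejection when NBP does nothing.**

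- 15% / 25%: the bias is 0.225 × 0.10 = 0.0225 SD, so z = 0.0225 / 0.0327 = 0.69. Rejection is Φ(−1.27) + Φ(−2.65) = 0.106. Across calculations the range is about 10-13%.
- 19% / 21%: the bias is 0.225 × 0.02 = 0.0045 SD, so z = 0.14. Rejection is about 5%; simulations gave 5-6%.

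**Second set of assumptions.** With 1200 per arm, correlation 0.7, the same recovery, and an effect reaching 25% / 50% / 100% of 0.10 SD:

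| Drop-out, control / NBP | LOCF: estimate, power | All visits: estimate, power |
|---|---|---|
| 20% / 20% | 0.0875, 78% | 0.100, 89% |
| 15% / 25% | 0.062, 49-50% | 0.100, 88% |
| 25% / 15% | 0.113, 94% | 0.100, 86% |

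With no effect and 15% / 25% drop-out either way, LOCF rejected 10-12% of the time and the all-visit estimate about 5%.

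**Where the gain comes from.** In a re-run at 1500 per arm, observed week-24 scores with a baseline covariate and no filling gave 0.100 SD and 86% power at 20% / 20% (all visits 90%), and 0.101 SD and 86% at 15% / 25% (all visits 88%). Adding the baseline covariate while keeping LOCF gave only 51% at 15% / 25%.

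**The case against.** A reader might infer that the estimate is biased whenever patients leave during recovery, that it always understates NBP, or that choosing the 24-week change is itself the fault. The documents support none of these.

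- **Leaving during recovery is not enough.** With 20% drop-out in both arms and a constant 0.10 SD effect, a simulation of the planned test gave 0.099 SD and 87% power, against 89% for all visits. With no effect it rejected 4%.
- **The direction can reverse.** If control loses more patients, LOCF overstates the effect.
- **The 10-point gap in drop-out has no source.** Interventions mentions only a few cases of transaminase elevation, and Sample size gives one overall figure. The documents also give no recovery figure after week 6. The remark in Discussion about unreliable early testing concerns a study at 1 month, so it does not supply one.
- **The 24-week change is the named endpoint and a legitimate target.** The weakness is how missing values are filled and that baseline is not adjusted for.
- **Other analyses are planned.** The per-protocol set largely avoids carried-forward week-24 scores.

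The first four points stand and limit the claim. The last mitigates without curing: the per-protocol set is a selected group of completers, the regression and the improved/unimproved split use the same change, the paired tests compare visits within an arm, and the Kaplan-Meier and Cox analyses use diagnoses.

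**Conclusion.** The point holds as a conditional one about a secondary outcome. The article itself fixes LOCF and an unadjusted change test for the main analysis, so this is not detail left to an analysis plan. Bias requires an effect that varies over time, which the 3-to-6-month outcome window makes plausible, or drop-out that differs between arms in amount or timing while scores are moving.

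Under the assumed growing effect and equal 20% drop-out, the estimate falls by 15% (0.015 / 0.100) and power by roughly 11 to 16 points (89 − 78 in the second set; 89 − 73 at most in the first). Under unequal drop-out the error can go either way. Inflated false rejection is material only with a sizeable gap between arms. These sizes are illustrations, since recovery, correlations, effect path and the gap are all assumed. The simulated drop-out also ignores scores, which favours the repeated-measures model.

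**What to change.** For MoCA-BJ and ADAS-Cog-C, and for HAMD-17 and ADL if they are analysed as change, make the main comparison a mixed model for repeated measures:

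- outcomes at weeks 6, 12 and 24;
- arm, visit, arm-by-visit, and baseline score by visit;
- unstructured covariance and no filled-in values;
- the week-24 arm difference reported with its 95% interval.

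Keep the LOCF change test as supportive only. Discussion ties some drop-out to cognitive state, and the model assumes data missing at random given the observed scores, so add one sensitivity analysis for data not missing at random.

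The cost is a change of wording and modest extra analysis on data already scheduled. Most of the gain comes from dropping LOCF and adjusting for baseline. The intermediate visits add about 2 to 4 points of power in the re-run above and allow for drop-out that depends on observed scores. Design states that recruitment was not complete at submission; the change should be fixed before outcome data are compared by arm.

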### Primary outcome

The primary outcome is the difference of incidence of delayed-onset PSCI between two groups after 24 weeks. We here define delayed-onset PSCI as cognitive impairment including mild cognitive impairment and dementia developed in 3–6 months after stroke, without early-onset PSCI. A group of trained neurologists who are blinded from allocation will make the final diagnosis at 24 weeks in the main center based on the Vascular Behavioral and Cognitive Disorders (VASCOG) criterion [25]. Mild cognitive impairment will be diagnosed based on 1) Concerns of a patient, knowledgeable informant, or a clinician of mild levels of decline in ≥1 cognitive domains from a previous level of cognitive functioning, and 2) Evidence of modest deficits in ≥1 cognitive domains on the neuropsychological testing (fall between 1 and 2 standard deviation below the mean (or between the third to 16th percentiles for test scores not normally distributed) of people of similar age, sex, education, and sociocultural background). And The cognitive deficits are not sufficient to interfere with independence (instrumental activities of daily living are preserved). Dementia will be diagnosed based on 1) Concerns of a patient, knowledgeable informant, or a clinician of significant levels of decline in ≥1 cognitive domains from a previous level of cognitive functioning, and 2) Clear and significant deficits in ≥1 cognitive domains on the neuropsychological testing (fall ≥2 standard deviation below the mean (or below the third percentile) of people of similar age, sex, education, and sociocultural background). And the cognitive deficits are sufficient to interfere with independence (e.g. at a minimum requiring assistance with instrumental activities of daily living).

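### If carried-forward scores feed the week-24 diagnosis, ITT patients last seen unimpaired at week 6 or 12 count as non-cases, so unequal or outcome-related drop-out biases the primary comparison in an unknown direction

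*Protocol article*

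**What the plan says.** The primary outcome is a yes/no diagnosis made by a blinded group at 24 weeks. The Primary outcome section defines it as "cognitive impairment including mild cognitive impairment and dementia developed in 3–6 months after stroke, without early-onset PSCI". The Secondary outcomes section defines early-onset PSCI as impairment arising within 3 months that then lasts at least 3 months. The Design section places cognitive testing at baseline and at weeks 6, 12 and 24.

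Statistical analyses defines the main population as "those who have a complete baseline assessment as well as at least one follow-up assessment for the primary outcome variables". On missing data it says only "Missing values of cognitive scores will be replaced by last observation carried forward method". It also plans a per-protocol analysis of patients who complete 24 weeks without major violations.

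The Sample size section allows for loss: "A drop-out rate of 20% was also considered, then 3000 cases in total were required". It gives no figure per arm. Two routes to drop-out are described. Under Interventions, raised transaminase after NBP leads to withdrawal of the drug and is counted as drop-out. Under Interventions and in the Discussion, starting an avoided drug, including one given for newly diagnosed dementia, is also counted as drop-out.

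**The concern.** The outcome window opens at about the time of the week-12 visit, and the only scheduled look inside it is week 24. A score carried forward from week 6 or 12 therefore says nothing about what happened in the window. If it is nevertheless used to settle the diagnosis, a patient who was unimpaired when last seen is recorded as free of delayed-onset PSCI. In effect this is a single imputation of no event, made without allowance for its uncertainty.

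The recorded incidence in each arm then depends on how many patients that arm lost, as well as on how many became impaired. In an open-label trial with one drop-out route tied to the study drug and another tied to the outcome, equal and uninformative loss cannot be taken for granted. The primary comparison could show a benefit that is not there, or hide one that is.

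**Working it through.** **Step 1. The plan's own figures.** The inputs are "4.4% of the incident rate and reduction of 50% were used in the end", so 4.4% against 2.2%; "Two-sided value of *p* < 0.05 will be considered significant"; and 1:1 allocation. The article states no power. With the pooled two-proportion formula,

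n per arm = [1.96 × √(2 × 0.033 × 0.967) + z(power) × √(0.044 × 0.956 + 0.022 × 0.978)]² / 0.022²

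this gives 1034 at 80% power, 1183 at 85% and 1384 at 90%. The stated 1200 per group gives 85.5% power, so it reproduces at an assumed power of about 85%. Then 1200 / 0.80 = 1500 per arm, or 3000 in total. The sample size itself is not at issue here.

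**Step 2. What carry-forward does.** Week 12 is day 84; 3 months is about 91 days (365.25 / 4).

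| Last seen | State at last visit | Status at week 24 if carried forward |
|---|---|---|
| Week 6 or 12 | Unimpaired | Unimpaired, so a non-case |
| Week 6 or 12 | Impaired since week 6 | Onset before 3 months; weeks 6 to 24 span 126 days, so early-onset and a non-case |
| Week 12 | First impaired at week 12 | Unclear: weeks 12 to 24 span 84 days, short of the 3 months that early-onset requires |
| No follow-up visit | Not assessed | Outside the main population, not scored |

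**Step 3. Size of the bias.** These are assumptions, because the article gives no drop-out by arm. There is no drug effect, incidence is 4.4% in both arms, 1500 are randomised per arm, loss is unrelated to outcome, and all carried-forward patients are scored as non-cases. Let d be the drop-out in an arm and f the share of lost patients who have a follow-up visit and so stay in the main population:

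recorded incidence = 0.044 × (1 − d) / (1 − d + f × d)

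Analysed numbers are 1500 × (1 − d + f × d). A false benefit is a significant result favouring NBP in the two-sided 0.05 test (z test equivalent to χ²); its nominal chance is 2.5%.

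| Drop-out control / NBP | f | Control | NBP | RR | False benefit |
|---|---|---|---|---|---|
| 20 / 20% | 1 | 3.52% | 3.52% | 1.00 | 2.5% |
| 18 / 22% | 1 | 3.61% | 3.43% | 0.95 | 4.5% |
| 15 / 25% | 1 | 3.74% | 3.30% | 0.88 | 9.6% |
| 15 / 25% | 0.5 | 4.04% | 3.77% | 0.93 | 5.5% |
| 15 / 25% | 0 | 4.40% | 4.40% | 1.00 | 2.5% |
| 10 / 30% | 1 | 3.96% | 3.08% | 0.78 | 25.7% |
| 10 / 30% | 0.5 | 4.17% | 3.62% | 0.87 | 10.8% |
| 25 / 15% | 1 | 3.30% | 3.74% | 1.13 | 0.4% |

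Worked line, 15/25% with f = 1: 0.044 × 0.85 = 3.74% and 0.044 × 0.75 = 3.30%. The difference is 0.44 points, its standard error is 0.673 points, and 0.44 / 0.673 = 0.65. The chance of exceeding 1.96 is 1 − Φ(1.96 − 0.65) = 9.6%.

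**Step 4. Under the planned effect.** With a true RR of 0.50 and f = 1, equal 20% drop-out keeps RR 0.50 (3.52% against 1.76%) and power 85.3%. At 15/25% the recorded RR is 0.44. At 25/15% it is 0.57 and power falls to 69.4%.

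**The case against.** The strongest reply is that LOCF is stated for cognitive scores, and change in those scores is a separate secondary outcome. The primary outcome is a panel diagnosis that also needs a reported concern and a judgement on independence, and nothing says these are carried forward. A rule for a missing diagnosis may sit in an analysis plan not shown. This stands in part: carrying the diagnosis forward is an inference. But the diagnosis rests on test scores, a single follow-up visit admits a patient to the main analysis, and LOCF is the only missing-data rule stated.

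Three stronger readings are tempting, and the article does not support them.

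- A reader might infer that every patient lost before week 24 is scored event-free, so that 20% loss cuts control incidence to 3.52% by construction. Patients with no follow-up assessment are excluded, which shrinks the bias.
- A reader might infer that carry-forward can never produce a delayed-onset case. A patient first impaired at week 12 has no clear class, and a late week-12 visit could fall after 3 months; the Discussion itself calls the visits about 1, 3 and 6 months.
- A reader might infer that the bias favours NBP. Transaminase withdrawals would push that way, but the article reports only a few such cases, which does not establish gaps of 10 or 20 points. Drop-out for dementia drugs can remove true cases from either arm and, if NBP works, more from control, which biases against NBP.

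Two further points stand. The article does not say whether a patient labelled a drop-out is still assessed at week 24. And the per-protocol analysis carries no week-24 visit forward, so it is a partial check, though it selects completers and does not protect the main analysis.

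**Conclusion.** The concern holds in a conditional form. On the natural reading of the stated rules, patients in the main population last seen unimpaired at week 6 or 12 become non-cases on the primary outcome, those first impaired at week 12 cannot be classified, and those with no follow-up visit leave the analysis after randomisation. Drop-out that differs by arm or is related to the outcome then biases the primary comparison.

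Neither size nor direction can be fixed from the article. With no drug effect, a ten-point gap in drop-out moves the risk ratio to 0.88 or to 1.13 depending on which arm loses more, if all lost patients are carried forward; the 0.88 becomes 0.93 if only half were seen again. If drop-out is equal and unrelated to outcome, the risk ratio is unbiased. These are illustrations that depend on assumed drop-out by arm, an assumed share with a follow-up visit and the planning rate of 4.4%; they are not predictions. The point still merits a change, because it touches the main analysis of the primary outcome.

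**What to change.** For the primary outcome:

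- Do not use LOCF, and state how a missing week-24 diagnosis is handled.
- Analyse all randomised patients, including those with no follow-up visit.
- Use any week-24 assessment obtained after a patient has been labelled a drop-out.
- Multiply impute missing week-24 status by arm from baseline, week-6 and week-12 data.
- Add a tipping-point sensitivity analysis that varies the drop-outs' event rate separately in each arm.

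For change in MoCA and ADAS-Cog, replace LOCF with a mixed model for repeated measures on the observed visits.

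The cost is revised analysis wording, some extra programming and slightly wider confidence intervals. No extra patients are needed. The article reports recruitment as incomplete at submission, so on that status the rule could be changed before results are seen.
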